## Abstract

**Background:**

Late onset sepsis is a frequent complication of prematurity associated with increased mortality and morbidity. The commensal bacteria of the gastrointestinal tract play a key role in the development of healthy immune responses. Healthy term infants acquire these commensal organisms rapidly after birth. However, colonisation in preterm infants is adversely affected by delivery mode, antibiotic treatment and the intensive care environment. Altered microbiota composition may lead to increased colonisation with pathogenic bacteria, poor immune development and susceptibility to sepsis in the preterm infant.

Probiotics are live microorganisms, which when administered in adequate amounts confer health benefits on the host. Amongst numerous bacteriocidal and nutritional roles, they may also favourably modulate host immune responses in local and remote tissues. Meta-analyses of probiotic supplementation in preterm infants report a reduction in mortality and necrotising enterocolitis. Studies with sepsis as an outcome have reported mixed results to date.

Allergic diseases are increasing in incidence in "westernised" countries. There is evidence that probiotics may reduce the incidence of these diseases by altering the intestinal microbiota to influence immune function.

**Methods/Design:**

This is a multi-centre, randomised, double blinded, placebo controlled trial investigating supplementing preterm infants born at < 32 weeks' gestation weighing < 1500 g, with a probiotic combination (*Bifidobacterium infantis, Streptococcus thermophilus *and *Bifidobacterium lactis*). A total of 1,100 subjects are being recruited in Australia and New Zealand. Infants commence the allocated intervention from soon after the start of feeds until discharge home or term corrected age. The primary outcome is the incidence of at least one episode of definite (blood culture positive) late onset sepsis before 40 weeks corrected age or discharge home. Secondary outcomes include: Necrotising enterocolitis, mortality, antibiotic usage, time to establish full enteral feeds, duration of hospital stay, growth measurements at 6 and 12 months' corrected age and evidence of atopic conditions at 12 months' corrected age.

**Discussion:**

Results from previous studies on the use of probiotics to prevent diseases in preterm infants are promising. However, a large clinical trial is required to address outstanding issues regarding safety and efficacy in this vulnerable population. This study will address these important issues.

**Trial registration:**

Australia and New Zealand Clinical Trials Register (ANZCTR): ACTRN012607000144415

The product "ABC Dophilus Probiotic Powder for Infants^®^", Solgar, USA has its 3 probiotics strains registered with the Deutsche Sammlung von Mikroorganismen und Zellkulturen (DSMZ - German Collection of Microorganisms and Cell Cultures) as BB-12 15954, B-02 96579, Th-4 15957.

## Background

### The intestinal microbial community and probiotics

Late onset sepsis (> 48 hours after birth) is a frequent complication in very preterm infants with high mortality and morbidity. In 2003, the Australian and New Zealand Neonatal Network (ANZNN) reported an incidence of 23% in very low birth weight infants (VLBW, less than 1500 grams) and 31% in extremely low birth weight infants (ELBW, less than1000 grams), with 18% mortality [1]. Preterm infants are more susceptible to infection as they have an immature immune system, which may in part be due to the abnormal development of their gastrointestinal microflora (microbiome). Molecular microbiological studies estimate that the mature human intestinal microbiome encompasses several hundred species of microorganisms with concentrations approximating 10^12 ^viable microbes per gram of faecal content [2]. This microbiome performs numerous important functions, including the digestion of macro and micronutrients, regulation of host fat storage, the metabolism of endogenous and exogenous compounds, immunoregulation and limiting colonisation with pathogenic microbes [3,4]. Disturbance of the gastrointestinal tract microbial environment may predispose individuals to a variety of diseases ranging from inflammatory bowel disease to allergy and obesity [4-7].

Colonisation of the aseptic intestine occurs rapidly after birth in healthy term infants. The intestinal microbial community is acquired from the birth canal and close parental contact after birth and is subsequently modified by diet [8]. Preterm infants acquire colonizing bacteria from the intensive care environment rather than their mother's vaginal canal, skin surface and milk [9]. Caesarean section delivery may delay infants' acquisition of diverse commensal flora by up to a year compared to vaginally delivered infants [10] and delivery by caesarean section occurs more frequently in preterm births (> 50% caesarean section rate for VLBW infants) [11]. These infants often receive antibiotics perinatally to prevent acute sepsis, and after birth for clinically suspected or definite culture positive sepsis, which further alters the composition of intestinal bacteria. Microbial diversity in the intestine of preterm infants, as assessed by culture-dependent methods, decreases with prolonged hospitalization [9,12-14]. Preterm infants also have delayed colonization with healthy commensals, such as *Lactobacillus *and *Bifidobacterium *species, which may lead to altered function of the gut microbial community, particularly the immune functions [9,15-19].

Probiotics are defined as live microorganisms, which when administered in adequate amounts may confer health benefits on people with specific illnesses [20]. Postulated mechanisms by which they may protect the host from gastrointestinal and urinary infections include: increasing resistance of the mucosal barrier to migration of bacteria and their toxins by strengthening intestinal cell junctions, modification of host response to microbial products, augmentation of immunoglobulin A mucosal responses, enhancement of enteral nutrition to inhibit the growth of pathogens; production of bacteriocins (small proteins which kill bacteria); and competitive exclusion of potential pathogens [21-25]. It has been hypothesized that very preterm infants, who have less microbial diversity in their GIT, may benefit from colonization with exogenously administered probiotics. Depending on the strain(s) administered, these probiotics could potentially induce a similar microbial community to that of the term infant or adult gastrointestinal microbiome [25]. The mechanisms by which probiotics may prevent the development of allergic disease are suggested to include all of the probiotic effects listed above as well as the induction of immune regulatory pathways

### Evidence from clinical trials of probiotics for prevention of sepsis and NEC in preterm infants

Several meta-analyses and systematic reviews of randomised controlled trials (RCTs) of probiotic use in preterm infants have been published in recent years [26-29]. The most promising results relate to supplementation with probiotics to prevent necrotising enterocolitis (NEC) and to reduce all-cause mortality.

Necrotising enterocolitis (NEC) is a relatively rare complication of prematurity. The incidence is inversely related to gestational age at birth. Overall, 88% of all reported cases in Australia in 2005 occurred in infants born before 32 weeks of completed gestation [1]. It is the most serious gastrointestinal problem of preterm infants and can rapidly progress from gastrointestinal dysfunction to bowel perforation and death in those most severely affected. Worldwide, the incidence is reported to be 1-3/1,000 live births and NEC affects approximately 10% of preterm infants born weighing less than1,500 grams [30]. Of those seriously affected, about half will require surgery to repair or excise diseased gastrointestinal tract and 25% will die. Long-term morbidity in survivors includes intestinal strictures, poor nutritional status and neurodevelopmental impairment [31-33]. No specific treatment exists for NEC; generally enteral feeds are ceased, with the administration of intravenous nutrition and broad spectrum antibiotics.

Cultivation and molecular-based studies have demonstrated quantitative and qualitative changes in faecal flora in the NEC prodrome; however, no single causative organism has been identified. Suggested pathogens have included bacteria (*E. coli, Clostridia perfringens, Enterobacter cloacae*, etc.), viruses (rota-, adeno-, corona-, noro-, etc.) and fungi (*Aspergillus *and *Mucor *spp.) [12,13,16,34-36]. NEC affected infants have also been shown to have lower species diversity in their gastrointestinal tract and this may limit the ability of their microbiome to perform its important immunoprotective functions.

The most recently published systematic review in 2,842 preterm infants concluded that enteral probiotic supplementation significantly reduces the incidence of severe NEC (Bell stage II or more) (typical RR 0.35, 95% CI 0.24 to 0.52) and mortality (typical RR 0.40, 95% CI 0.27 to 0.60) [29,37]. Other studies investigating probiotic use in very preterm infants have also reported favourable effects on the incidence of NEC, time to full enteral feeds, weight gain, colonisation rates and immune responses in the probiotic versus placebo group [38-43].

These studies support the hypothesis that augmentation of the intestinal microbiome of premature infants with exogenous probiotics (healthy organisms) may favourably alter the microflora resulting in an improvement in clinical outcomes. While these results are very promising, debate continues regarding the routine use of probiotics in preterm infants [44-46]. Many trials in these meta-analyses do not include the most vulnerable preterm infants, those born weighing less than 1,000 grams and before 28 weeks' gestation. In addition, there is a lack of data regarding the optimal strain(s), dose, time to start and duration of probiotic therapy, as well as the taxonomy and quality of currently available probiotics formulations and products. Further large clinical trials using products registered with microbial culture banks (for quality assurance) are required to resolve these issues and to support the development of probiotic products of pharmaceutical quality. Probiotic supplementation has not yet been evaluated in a population of Australian very preterm infants.

Results of studies investigating the use of probiotics to reduce the incidence or severity of sepsis have been equivocal. The Cochrane Database systematic review found no evidence of significant reduction of nosocomial sepsis (typical RR 0.90, 95% CI 0.76 to 1.07) [29], although some of the earlier individual RCTs demonstrated a difference in sepsis rates between probiotic and placebo groups [47,48]. The lack of effect reported in the Cochrane review may be due to the heterogeneity of the RCTs included in the review with regard to the variation in probiotic strains studied, the method of administration (dosage, frequency, duration, etc.) or differences in local nursery guidelines for the diagnosis and treatment of sepsis. Also, the sub-group of ELBW preterm infants who are most susceptible to late onset sepsis is under-represented as only small numbers of them were recruited to published trials.

These issues are being addressed by this large (1,100 participants), multi-centre, randomised, double-blinded, placebo controlled trial, which has adequate power to demonstrate clinically significant effects of the chosen probiotic mixture on the rate of late-onset sepsis in VLBW infants but not on NEC. It is also sufficiently powered to demonstrate any significant adverse effects in infants below 1000 g birth weight and less than 28 weeks' gestation.

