### Conduct of the trial

#### • Randomisation

This is achieved using variable block design constructed by the Clinical Epidemiology and Biostatistics Unit (CEBU) at the Murdoch Children's Research Institute, who are independent of the study investigators. Each block contains equal numbers of placebo and active allocation. Randomisation is stratified by unit. Each of the participating neonatal units is able to access the next sequentially numbered probiotic or placebo immediately after randomisation. Records are kept and audited to check that sequential randomisation is used to assign infants to either study group. All doctors, nurses, research assistants, laboratory staff and parents are blind to the randomised allocation. The key is held by the Chief Pharmacist at The Royal Women's Hospital and the trial statistician, both of whom are independent of the investigators and not involved in outcome assessment.

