### Statistical Aspects and Consideration

#### • Sample size calculation

Statistical advice has been provided on all aspects of study design, sample size and analyses by CEBU, who will assist in analysis at trial completion.

To reduce the incidence of culture proven sepsis from 23% to 16% (a 33% reduction) with a power of 0.8, α of 0.05, and a 2-tailed test, the estimated sample size is 530 per group. The trial will therefore recruit 1,100 infants over 5 years, based on our experience that 50% of parents consent to participation in this preterm population.

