Whilst the above findings appear promising, debate continues regarding the routine use of probiotics in this vulnerable population [44-46]. Further large clinical trials using products registered with microbial culture banks (for quality assurance) are required to support the development of probiotic products of pharmaceutical quality. This large multi-centre, randomised, double blinded, placebo controlled trial has adequate power to demonstrate clinically significant effects of the chosen probiotic mixture on the rate of late-onset sepsis in VLBW infants. It is also sufficiently powered to demonstrate any significant adverse effects in infants below 1000 g birth weight and less than 28 weeks' gestation. More than 900 infants have been enrolled to date, therefore, we are on course to reach our target recruitment number of 1,100 participants and anticipate that results will be available in early 2012.

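### The unqualified claim of power to show any significant adverse effect in infants below 1000 g and 28 weeks is not supported by the design

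*Protocol article*

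**What the plan says.** The claim appears twice in the protocol article. It closes the Background section on trials of probiotics for sepsis and NEC, where the trial is described as "sufficiently powered to demonstrate any significant adverse effects in infants below 1000 g birth weight" and under 28 weeks' gestation. The last paragraph of the Discussion repeats it: "It is also sufficiently powered to demonstrate any significant adverse effects in infants below 1000 g birth weight", with the same gestational limit. Neither place names an adverse outcome, an event rate or a size of effect.

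The Background sentence just before the claim says that the trial has adequate power for late-onset sepsis in VLBW infants but not for NEC. An earlier paragraph of the same section puts NEC at about 10% of infants below 1500 g.

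The section on sample size calculation holds the only power calculation. It concerns culture-proven sepsis falling from 23% to 16% in the whole trial population: "with a power of 0.8, α of 0.05, and a 2-tailed test, the estimated sample size is 530 per group". It continues: "The trial will therefore recruit 1,100 infants over 5 years". Under Randomisation, allocation is equal: "Each block contains equal numbers of placebo and active allocation". The inclusion criteria admit infants below 1500 g and under 32 weeks, so those below 1000 g and 28 weeks are only part of the 1,100.

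**The concern.** A trial sized to give 80% power for one 7-point difference in one common outcome, using all its infants, cannot also be powered for every important adverse effect in a part of them. The two adjoining Background sentences also sit badly together. The first concedes too little power for NEC in the whole trial. The second claims power for any significant adverse effect in a smaller group, in whom an increase in NEC would itself be a serious harm.

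What is at stake is how the safety results are read. The Background says that many earlier trials left out the most vulnerable preterm infants and that ELBW infants are under-represented in the sepsis evidence. The trial is presented as addressing these gaps. Set against a stated claim of sufficient power, a non-significant difference in this subgroup could be taken as evidence of safety when a clinically important increase has not been excluded.

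**Working it through.** **Inputs from the protocol article**
- Sepsis 23% versus 16%, power 0.80, two-sided α 0.05, 530 per group, 1,100 recruited (Sample size calculation).
- 1:1 allocation (Randomisation), so 550 per arm in total.
- Late-onset sepsis 31% in infants below 1000 g (first Background section).
- NEC about 10% in infants below 1500 g (Background, section on sepsis and NEC trials).

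**Assumptions, not in the article**
- Subgroup share of 30% to 60% of 1,100, that is 165 to 330 per arm.
- A 1% baseline to stand for an uncommon adverse event.
- The 10% NEC rate is for all infants below 1500 g and is carried over to the subgroup as an illustration.

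**1. The plan's own figure.** With p̄ = (0.23 + 0.16)/2 = 0.195 and d = 0.07:

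n = [1.96·√(2·0.195·0.805) + 0.8416·√(0.23·0.77 + 0.16·0.84)]² / 0.07² = 501.7, so 502 per arm.

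With the continuity correction, n′ = (n/4)·[1 + √(1 + 4/(n·d))]² = 529.9, so 530 per arm. The stated figure is reproduced exactly.

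**2. Power formula for the subgroup.** No continuity correction is used below, which favours the protocol:

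Power = Φ{ [ |p₂ − p₁| − 1.96·√(2·p̄·(1 − p̄)/n) ] / √[ (p₁(1 − p₁) + p₂(1 − p₂))/n ] }

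**3. Worked case: the trial's own 7-point difference, as harm on sepsis (31% to 38%).** Here p̄ = 0.345.
- n = 165: (0.07 − 0.1026)/0.0522 = −0.62, power 27%.
- n = 330: (0.07 − 0.0725)/0.0369 = −0.07, power 47%.
- n = 550 (every infant in the subgroup): (0.07 − 0.0562)/0.0286 = 0.48, power 69%.

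**4. Power for selected harms**

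| Harm | 165 per arm | 220 | 275 | 330 | 550 (all infants) |
|---|---|---|---|---|---|
| Sepsis 31% to 38% | 27% | 34% | 41% | 47% | 69% |
| Sepsis 31% to 46.5% (RR 1.5) | 83% | 92% | 96% | 98% | >99% |
| 10% event to 15% | 28% | 35% | 43% | 49% | 71% |
| 1% event to 2% (assumed) | 11% | 14% | 16% | 18% | 28% |

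**5. Smallest increase detectable with 80% power** (the formula solved for p₂)

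| Baseline | 165 per arm | 220 | 275 | 330 |
|---|---|---|---|---|
| Sepsis 31% | 46.0% (RR 1.48) | 43.9% (RR 1.42) | 42.5% (RR 1.37) | 41.5% (RR 1.34) |
| 10% event such as NEC | 21.1% | 19.4% | 18.3% | 17.5% |
| 1% event (assumed) | 7.0% | 5.8% | 5.1% | 4.6% |

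The normal approximation is rough for the 1% event, where only about 2 to 3 events per arm are expected at baseline (165 × 0.01 = 1.65; 330 × 0.01 = 3.3). That row gives the order of size only.

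**6. Dependence on the assumed share.** Power rises with n, and n cannot exceed 550 per arm. The last column of the table in step 4 is therefore a ceiling. Three of its four rows stay below 80%, so the unqualified claim fails at every possible share.

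**The case against.** The strongest defence is that the subgroup is not helpless. The trial is sized for a ratio of 23/16 = 1.44 on sepsis. The sepsis increase detectable in the subgroup is RR 1.34 to 1.48, about the same relative size, and power for RR 1.5 is 83–98%. This stands. A reader might infer from the tables that the design can show no harm at all in these infants, or only extreme harm. For common outcomes such as sepsis the figures do not support that.

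Some further points also limit the concern.
- A journal article commonly leaves subgroup sizes and safety outcomes to the full protocol. Their absence is therefore not the defect. The defect is an affirmative statement that the stated design cannot bear.
- The sentence may mean clinically important effects, and its weight and gestation limits may describe two overlapping groups rather than infants meeting both. Neither reading rescues it: a 7-point rise in sepsis is the absolute size of difference that the trial was sized for, and the claim fails even with all 1,100 infants.
- A reader might infer that a null result would be misread, or that safety monitoring rests on this sentence. The article sets no subgroup safety test and no decision based on a null subgroup result. It provides an independent data monitoring committee, with full interim analyses at 100, 400 and 700 infants and a further look at mortality at 200. Only 'could be misread' is supported.
- The first Background section also gives an 18% mortality figure, but it is unclear to which infants it refers. No result here depends on it.

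**Conclusion.** The concern holds as a point about an unqualified claim. The article twice states a power that the design does not have. The sole calculation covers sepsis in the whole trial, and it reproduces exactly, so there is no error in the sample size itself.

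At an assumed 165–330 per arm, 80% power is reached only for absolute increases of about 10 to 15 points in sepsis from 31% (41.5 − 31 = 10.5; 46.0 − 31 = 15.0), and of about 7.5 to 11 points in a 10% event (17.5 − 10 = 7.5; 21.1 − 10 = 11.1). The sizes rest on the assumed share and, for uncommon events, on the assumed 1% rate. The conclusion does not: with all 1,100 infants, power is still 69% for sepsis 31% to 38%, 71% for a 10% event rising to 15%, and 28% for a 1% event doubling.

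Severity is moderate. The sentence stands in the Background and Discussion and drives no sample size, endpoint or stopping decision. It does, however, concern the infants whom the article calls the most vulnerable.

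**What to change.** Delete the sentence in both the Background and the Discussion. Alternatively, replace it in both places with three statements:
1. the sponsor's own expected number of infants per arm in the subgroup, saying whether both limits must be met;
2. the difference detectable with 80% power for each named safety outcome, calculated from that number;
3. that subgroup safety results are estimates reported with 95% confidence intervals, and that a non-significant difference does not exclude harm.

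The figures should come from the sponsor's expected subgroup size, not from the 30–60% range assumed here. The cost is wording only: no added infants, data or analyses. A stated property of the trial becomes less favourable.

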### Evidence from clinical trials of probiotics for the prevention of allergic disease

An epidemic rise in allergic disease in "westernised" countries, especially food allergy and asthma, has occurred in parallel with many lifestyle changes [49]. Studies have linked alterations in the intestinal microflora in infants with the later development of allergic disease [50-52]. These abnormalities particularly involved *Bifidobacterium *species [53-57] and microbial diversity [12]. Probiotics are capable of inducing an intestinal microflora composition similar to that of a healthy breastfed term infant [58]. Therefore, they may have the potential to reduce allergic diseases by "normalising" the gastrointestinal tract microflora. Probiotics can also modulate immune function by altering dendritic cell [59], regulatory T cell [60,61], and T helper cell responses [62]. A Cochrane Library meta-analysis of probiotic supplementation for the prevention of allergic disease in term infants found a significant reduction in eczema in infants who received probiotics compared with those that did not [typical RR 0.82, 95% CI 0.70, 0.95] and further trials were recommended to determine the reproducibility of the results [63].

A more recent review and meta-analysis reported that a protective effect against allergic disease was only observed if probiotic supplementation were initiated in the prenatal period and continued postnatally, but not if probiotic supplementation were commenced postnatally [64]. However, there were only 4 small studies that administered probiotics postnatally, with 1 of these 4 studies reporting a beneficial effect from postnatal supplementation [65-68]. Therefore, further studies are required to determine if postnatal administration of probiotics might be beneficial for prevention of allergic disease.

